### Statistical methods

#### POSAS (Version 2)

Participants are analysed in trial arm they were initially randomised to regardless of whether treatment was completed (intention-to-treat analysis). Significance tests are 2-sided at the 5% level. Patient component of the POSAS scale at 6 months is the primary outcome measure. In the main analysis, mean POSAS scores at 6 months is compared between trial arms using multiple regression with treatment arm, study site (a design variable) and burn location (a stratification variable coded as (1) head/neck, (2) torso or (3) limbs) as factors and baseline patient POSAS and current age as co-variates. A similar approach will be used for secondary outcome analyses.

For the primary outcome, additional analysis will:

consider patient POSAS over all 4 time points (baseline, 6 week, 12 week and 6 months) using a multi-level/mixed model.use multiple imputation to assess the impact of missing data.conduct per-protocol and Complier-Average Causal Effect (CACE) analyses based on completion of the 3 laser sessions.

Prior to the completion of data collection, a detailed statistical analysis plan will be developed and signed off by the CI and TSC.

#### Additional analyses

A similar approach will be used for secondary outcome analyses.

##### Colour analysis

The difference in measured value E (erythema) between the tested and normal area is used as the outcome measure^
72
^. A reduction in redness value will indicate an improvement to the scar; a surrogate of inflammation. This value can be correlated against the POSAS for colour or redness.

##### Economic analysis

There is paucity of economic evidence for burn scar treatment. A within-trial economic evaluation is conducted to assess the cost-effectiveness of PDL. The primary analysis is cost-utility analysis from NHS and Personal Social Services perspective. An incremental analysis will compare the differences in costs and Quality Adjusted Life Years (QALY) between SoC and PDL. An exploratory analysis using a societal perspective is performed to capture broader impacts of burns treatment. The SF-6D algorithm is applied to calculate QALY gained^
73
^. The economic evaluation follows best-practice guidelines.

##### Qualitative analysis

Individual interviews are audio-recorded and then transcribed verbatim. These anonymised transcripts are analysed thematically using the Braun and Clarke process of thematic analysis^
74
^. The analysis is inductive; grounded in the participants’ experiences. The process includes familiarising oneself with the data through repeated reading, searching for meanings and patterns within each focus group/interviews by the qualitative researcher. This leads to the identification of initial codes within each of the interviews, and initial themes from reviewing the codes across the whole data set. Following this, a review of themes leads to the finalisation of the qualitative themes. These are shared and explored across the research team and Patient Advisory Group to ensure both cognisance with the raw data and credibility of the analysis process.

#### Analysis population and missing data

The main analysis will analyse participants in the group to which they were randomised, regardless of the treatment they actually received. No imputation of missing data will be used for the main analyses, but multiple imputation of missing data will be conducted in additional analyses for the primary outcome. Further details of the approach to be used will be described in a detailed statistical analysis plan

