The PPI group suggested that they would be willing to wait at least 6 months for laser intervention but would not be willing to forego treatment entirely. There are ethical concerns regarding completely depriving patients of PDL as this is part of “standard” burns care at some sites. Similarly, recruitment to the trial would be difficult if the alternative to not being in the trial was to be given PDL treatment.

Finally, there is the issue of loss of patients to follow-up as a result of waning compliance if they have a positive result with PDL intervention; attrition of patients in longitudinal burns studies is a common issue which can confound trials^
58
^. The authors have allowed for attrition in our sample size calculation.

Standard interval between treatment sessions for PDL is usually 4 – 6 weeks. The bruising resulting from the treatment subsides within 2 – 3 weeks and the effect of the treatment is evident at this point. For this trial, there is around 3 months between the last treatment and measurement of outcome at the primary end-point. This primary endpoint therefore allows a reasonable duration of time for laser treatment to have an observed effect.

It is acknowledged that this is a relatively short follow-up period given that the duration of scar maturation can take upwards of 2 years. A longer-term outcome than 6 months would prove interesting, but the authors hypothesise that a shorter-term improvement would serve to “flatten the curve” of scar maturation, expedite the scarring process and eventually lead to an improved scar outcome. Even at this time point, this may translate as a clinical efficiency and saving for the NHS by a reduction in follow-up appointments and cost of further scar revision; thus justifying the study from the perspective of clinical efficiency.

The 6 month follow-up strikes a compromise between reliable data on scar outcome and a suitable residual size of cohort from which to draw reliable conclusions. It is also a compromise between ensuring a reasonably long follow-up for treatment to show effect and having a research design that was acceptable to potential participants. It is concluded that having a 6 month follow-up is long enough to show any benefits of PDL, but short enough to counter ethical and recruitment concerns.

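### The main analysis ignores interim patient POSAS scores although the protocol names loss of PDL responders as a risk, so the PDL effect could be biased towards zero

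*Protocol article*

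**What the plan says.** Under Statistical methods, POSAS (Version 2), the main comparison is a multiple regression of the 6-month patient score. Arm, site and burn location enter "as factors and baseline patient POSAS and current age as co-variates". No post-baseline score enters the model.

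Under Analysis population and missing data, the rule is: "No imputation of missing data will be used for the main analyses". The same sentence goes on to plan multiple imputation, but confines it to additional analyses of the primary outcome. A second additional analysis will "consider patient POSAS over all 4 time points (baseline, 6 week, 12 week and 6 months) using a multi-level/mixed model".

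Under Follow-up duration, the protocol raises "loss of patients to follow-up as a result of waning compliance if they have a positive result with PDL intervention", notes that attrition can confound burns studies, and replies: "The authors have allowed for attrition in our sample size calculation". The same section uses the point to justify a short follow-up: "The 6 month follow-up strikes a compromise between reliable data on scar outcome and a suitable residual size of cohort".

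Under Sample size, 120 analysed participants become 150 recruited, to allow for 20% dropout. Under Retention, missed visits are rearranged. Failing that, outcomes are sought by telephone with the primary outcome first, and good retention is anticipated.

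**The concern.** The protocol describes a loss mechanism that depends on response and acts in one arm, yet its main analysis is unbiased only if missingness is unrelated to the 6-month score once arm and the baseline covariates are taken into account. Recruiting 150 rather than 120 restores the number analysed. It does nothing about which participants are missing. Baseline adjustment does not help either, because the selection would act on change after baseline.

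Patient POSAS is measured at weeks 0, 6, 12 and 26 (Table 2), so someone lost after week 12 usually has two informative follow-up scores. The main analysis leaves them unused.

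Under this mechanism the bias runs against PDL. The Dissemination section says that NHS provision of PDL may be revised if it proves ineffective, so an understated effect would bear directly on that decision.

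**Working it through.** **Inputs from the protocol (Sample size).** Difference 6, SD 10, two-sided 5%, 90% power, 60 per arm, 20% dropout, baseline to 6-month correlation 0.545.

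**The protocol's own figures reproduce.**
- n per arm = 2(1.96 + 1.2816)² × 10² / 6² = 58.4, so 59; the protocol uses 60. Power at 60 per arm is 90.8% (normal approximation) or 90.3% (noncentral t).
- 120 / (1 − 0.20) = 150.
- With baseline adjustment, residual SD = 10 × √(1 − 0.545²) = 8.38. At 60 per arm, power for 5 points is 90.4%.

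**Bias by algebra.** Let d be the proportion of PDL participants without a 6-month score, and k the number of points by which their unseen scores are better than those of PDL completers. Suppose control dropout is uninformative. The whole PDL arm is then d × k better than its completers, so the complete-case effect is 6 − d × k. The values of k are assumptions; d = 0.20 takes the overall dropout allowance as applying to the PDL arm. Power is the normal approximation at 60 per arm with SD 8.38, so the standard error is 8.38 × √(2/60) = 1.53.

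| k | Complete-case effect | Baseline-adjusted power |
|---|---|---|
| 0 | 6.0 | 97.5% |
| 2 | 5.6 | 95.5% |
| 4 | 5.2 | 92.5% |
| 6 | 4.8 | 88.0% |
| 10 | 4.0 | 74.3% |

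**Bias by simulation.** One million patients, 20% dropout per arm. Control dropout is random; PDL dropout has log-odds rising by 0.5, 1 or 2 per SD of improvement. Assumed, not from the protocol: baseline to week-12 correlation 0.545, week-12 to week-26 correlation 0.7, week-12 effect 3, and the selection slopes. The imputation is a single regression imputation by arm on baseline and week-12 POSAS, standing in for multiple imputation. The true effect is 6.

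| PDL dropout driven by | Complete-case effect (slopes 0.5, 1, 2) | Using week-12 score |
|---|---|---|
| Change to week 12 (observed) | 5.6, 5.3, 4.9 | about 6.0 throughout |
| Change to 6 months (unseen) | 5.3, 4.7, 4.0 | 5.5, 5.1, 4.5 |

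**Dependence on the control arm.** If control improvers leave in the same way, the complete-case effect stays at 6.0 for every slope and both drivers. If control non-improvers leave instead, it falls further: to 5.2, 4.5 and 3.7 when dropout depends on change to week 12.

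**What week 12 can and cannot show.** Three sessions 6 weeks apart, with about 3 months from the last to the endpoint, put the third session near week 12. Laser follows assessment at a visit (Interventions). The week-12 score is therefore taken before any response to the third session. A patient who leaves because of the completed course leaves on information that no interim score holds. The second row of the table is then the relevant one.

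**The case against.** A reader might infer that the protocol expects PDL responders to drop out and that the main result would therefore be biased. The text does not go that far. Follow-up duration raises the issue as a risk while defending a 6-month endpoint, with no rate and no pattern by arm. The 20% is a general allowance. Retention anticipates few losses and provides for the primary outcome to be taken by telephone, so a responder who stops attending clinic need not have a missing score. The bias also needs one-sided selection, and no document gives dropout by arm. Controls are offered laser when participation ends, which may keep them attending, but patients who decline the trial get the same offer, so that argument is weak.

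A reader might also infer that the main analysis is the only planned one at risk, or that missing data are left unaddressed. Neither holds. Multiple imputation and a mixed model are both planned, with details left to the SAP. If dropout depends on response after week 12, they too recover only part of the effect.

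Nor do the figures support a claim that power collapses. With the planned baseline adjustment, an effect attenuated to 4.8 points still has 88% power, close to the design target. The main harm is a biased estimate; loss of power is secondary except under strong selection.

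These points reduce the certainty and size of the problem. They do not explain why the headline estimate should be the one that leaves observed interim scores unused, nor do they make a larger sample an answer to selective loss.

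**Conclusion.** The point holds as a conditional one. If PDL responders selectively lack 6-month scores and controls do not leave in the same way, the planned main estimate could be biased towards zero. The size is roughly 0.4 to 2 of the assumed 6 points at 20% dropout, under the assumed gaps, correlations and selection slopes above. It is zero if selection is equal in both arms, smaller if telephone collection succeeds, and larger if control non-improvers leave.

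The interim scores remove the bias if dropout depends on what was observed by week 12, and only part of it (4.5 to 5.5 recovered out of 6) if it depends on later response. The documents do not show that the bias will occur. They show that the protocol identified the risk and gave it an analytic answer that cannot deal with it, while a better one is already planned in a secondary role.

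**What to change.** Make the planned mixed model over all four patient-POSAS time points the main analysis, and report the 6-month treatment contrast, with baseline POSAS, site, burn location and age in the model. State how baseline enters: either as a response with a common mean in both arms, or as a covariate with the three follow-up scores as responses.

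If the regression must stay primary, run it after multiple imputation done separately by arm, with week-6 and week-12 patient POSAS in the imputation model.

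In either case, keep the complete-case regression as a sensitivity analysis. Add a missing-not-at-random sensitivity analysis, for instance one that shifts the imputed PDL scores by a range of values of k.

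The cost is wording in the protocol and SAP and a slightly more complex primary model. The mixed model and the imputation are already planned and the scores are already collected, so only the missing-not-at-random analysis is new. The change should be fixed before outcomes by arm are seen.

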### Ancillary and post-trial care

This is an NHS-sponsored research trial. If an individual suffers negligent harm as a result of participating in the trial, NHS indemnity covers NHS staff and those people responsible for conducting the trial who have honorary contracts with the relevant NHS Trust. In the case of non-negligent harm, the NHS is unable to agree in advance to pay compensation, but an ex-gratia payment may be considered in the event of a claim. Any harm to participants arising from the design or management of the research is covered by the NHS Litigation Authority. There are no arrangements for the Sponsor to pay compensation in the event of harm to research participants where no legal liability arises.

## Dissemination

The full study protocol will be published in NIHR Open Research. Results from this study will be disseminated to HCPs through both publications in the journal *Burns* and presentations at British Burns Association (BBA), European Burns Association (EBA) and/or International Society of Burn Injury (ISBI) annual meetings. The main publication will be submitted to *Burns Open* and this is costed in the budget. The main publication will be authored by the Trial Management Group, which consists of the co-applicants and principal investigators. The qualitative component of the RCT is published within a high impact journal such as *BMC* (*Open*). The participant level dataset and statistical code will be archived on the BU data repository BORDaR (https://bordar.bournemouth.ac.uk/)

If the study proves effectiveness of PDL, it could underpin the evidence for NICE guidelines of PDL burn scar treatment; if ineffective, the provision of PDL in the NHS may be revised. The evidence should improve how healthcare is delivered in line with the RfPB statement. The outcome of this study may be generalised for hypertrophic scars from surgery or other trauma.

The treatment protocol will be shared across the UK burns community through the Burns Operational Delivery Networks. Key study findings are relayed to burn scar participants and the wider patient group through lay summaries for burns support forums/websites, such as Dan’s Fund and TalkHealth. Details of the Patient and Public Involvement process and how this has shaped the study are submitted to a journal such as *Research Involvement and Engagement*.

## Study status

As of November 2021, the study is in final set-up stage for some sites and recruitment stage is imminent. The study database has been written on REDCap and is ready for use.

## Figures and Tables

**Table 1 T1:** Potential recruitment rates at each site in the trial.

Centre	Per annum	Over recruitment period (21 months)
Salisbury (CI site)	30	52
Chelsea & Westminster	50	88
Leeds/Scotland	45	79
Mid & South Essex	50	88
Newcastle	50	88
UH Birmingham	80	140
North Bristol	50	88
**TOTAL**	**355**	**621**
*East Grinstead*	*50*	*88*
** *TOTAL with added sites* **	** *405* **	** *709* **

**Table 2 T2:** Participant timeline over the course of the study.

	**STUDY PERIOD**					
	Enrolment	Allocation	Post-allocation			Close-out
TIMEPOINT	*-t_1_ *	0	*0 weeks*	*6 weeks*	*12 weeks*	*26 weeks*

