#### Concealment mechanism

At first visit, data required for randomisation is entered onto the system. Blinded personnel may enter data for randomisation as the allocation is not displayed on the screen and is only transmitted by e-mail to those specified. The treating healthcare professional will be informed of patient treatment allocation by the CTU via email to their @nhs. net account. The principal investigator at that site will be copied in to this email defining the allocation. Blinded personnel entering data will not receive this e-mail, but will be informed by the system that the randomisation has been successful and that the e-mail has been sent.

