### Outcomes

#### Primary outcome

Scar Quality - Patient-rated Patient Observer Scar Assessment Scale (POSAS version 2) score at 6 months (mean change from baseline).

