### Data collection

#### Blinding (masking)

Blinded assessments of observer-rated POSAS and colour measurement are performed by scar management HCPs prior to ± laser treatment. The participants are instructed not to divulge their allocation to HCP to maintain blinding. This means that both the observer-rated POSAS and colour measurement are conducted by someone blinded to treatment allocation.

The patient-rated POSAS (primary outcome) and the relevant QoL questionnaires are completed by the participant. Although this assessment cannot be blinded, it was felt, as informed by the PPI group, that the participant’s perspective should be paramount in this trial. It is accepted that this may bias the patient-rated POSAS result in that they will make their rating knowing to which treatment arm they had been allocated. However, blinded clinician-rated secondary outcomes are included. In addition, the data collection, statistical analysis and initial interpretation of the primary and secondary outcome results will be blinded.

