**ENROLMENT**:						
Eligibility screen	X					
Informed consent	X					
Patient Demographics & Burn History	X					
Allocation		X				

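### Table 2 places the baseline self-ratings (patient POSAS, CARe, SF-12) after allocation, and nothing requires them before randomisation or before the participant learns the arm

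*Protocol article*

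**What the plan says.** **Schedule.** Table 2 runs from Enrolment to Allocation (timepoint 0), and then to 0, 6 and 12 weeks under "Post-allocation", with close-out at 26 weeks. The first marks for POSAS, CARe and SF-12, colour and healthcare resource use are all in the 0-week column. Apart from allocation itself, the only items marked before that column are the eligibility screen, consent and "Patient Demographics & Burn History".

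**Order within the visit.** The Concealment mechanism section says: "At first visit, data required for randomisation is entered onto the system". It does not place this step before or after the questionnaires. The allocation goes by e-mail to the treating professional, with the site's principal investigator copied in. When the participant is told is not stated. The Blinding (masking) and Pulsed Dye Laser sections put assessment before laser treatment, not before randomisation.

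**Masking.** On patient-rated POSAS and the quality-of-life questionnaires, Blinding (masking) says: "Although this assessment cannot be blinded". It accepts possible bias because "they will make their rating knowing to which treatment arm they had been allocated". Of the assessor it says: "The participants are instructed not to divulge their allocation to HCP to maintain blinding".

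**Use of the baseline.** The main regression includes "baseline patient POSAS and current age as co-variates". The Primary outcome section defines the outcome as the patient-rated "score at 6 months (mean change from baseline"). A similar approach is planned for the secondary outcomes.

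**The concern.** Randomisation makes the arms comparable in expectation only on what is measured before allocation, or at least before allocation can influence the measurement. A self-rating made by someone who already knows the arm has no such protection. Disappointment at standard care alone, or hope raised by the offer of laser, could shift the score before any treatment is given.

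If that happened, adjusting for baseline would carry part of the shift into the treatment effect. If the laser arm rated its baseline scar better than it otherwise would, benefit would be understated; if worse, overstated. The plan accepts bias from unmasked patient rating in general but does not consider bias in the covariate.

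The planned mixed model over all four time points gives no independent check, because it includes the same baseline. CARe and SF-12 are collected only at baseline and 6 months, so the same question arises for quality of life and for QALYs derived from SF-12. A baseline collected in the wrong order cannot be collected again.

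**Working it through.** **1. Schedule.** POSAS has four marks, at 0, 6, 12 and 26 weeks, which agrees with the four study sessions in Participant timeline. The enrolment and allocation columns are empty in every assessment row. The placement is therefore coherent and not a broken table. The Eligibility criteria section fixes identification of the study scar before randomisation; no equivalent statement covers the baseline ratings.

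**2. The plan's own figures (Sample size section).** Difference 6, SD 10, two-sided 5%, 90% power:
- The normal approximation gives 59 per arm; t-test power at 60 per arm is 0.903.
- Dropout: 120 / (1 − 0.20) = 150.
- With correlation 0.545, the adjusted SD is 10 × √(1 − 0.545²) = 8.38. Power for 5 points at 60 per arm is 0.904.

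The stated figures reproduce, and this point changes none of them.

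**3. Effect of a baseline shift.** Let s be the between-arm difference in baseline rating caused by knowing the arm. Assume it does not carry over to the 6-month score and leaves the within-arm slope unchanged. Then:

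shift in adjusted effect (absolute size) = slope × s, with slope = r × SD(follow-up) / SD(baseline)

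- Equal SDs: slope = 0.545.
- SDs pooled by sample size. This pooling is ours; the plan itself states only an SD of around 10. Inputs are the service evaluation (15 patients; SD 10.6, then 11.2) and the silicone study (46 scars; SD 7.8, then 11.5).
  - Baseline: √[(14 × 10.6² + 45 × 7.8²) / 59] = 8.55
  - Follow-up: √[(14 × 11.2² + 45 × 11.5²) / 59] = 11.43
  - Slope: 0.545 × 11.43 / 8.55 = 0.73
- The 46 scars came from 23 patients. Weighting by patients (14 and 22 degrees of freedom) gives SDs of 8.99 and 11.38, and slope 0.545 × 11.38 / 8.99 = 0.69.

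**4. Illustration.** The documents give no value for s; 1 to 3 points is an assumed range. Shift in the adjusted effect:

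| Assumed s | Slope 0.545 | Slope 0.73 |
|---|---|---|
| 1 | 0.55 (9% of 6) | 0.73 (12%) |
| 2 | 1.09 (18%) | 1.46 (24%) |
| 3 | 1.64 (27%) | 2.19 (37%) |

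**5. Consequence for the test.** With 60 per arm and equal SDs, the standard error is 8.38 × √(2/60) = 1.531. For s = 1, 2, 3:
- With no true effect, the chance of a significant result is about 0.065, 0.11 and 0.19 instead of 0.05.
- If the shift hides benefit, power for a 5-point effect falls from 0.90 to about 0.83, 0.72 and 0.59.

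**The case against.** **Allocated is not the same as told.** The allocation is not shown on screen and is e-mailed only to the treating professional and principal investigator. A reader might infer from Table 2 that the baseline is in fact an unmasked rating. The documents do not support that: no section says when the participant learns the arm. The masking section's remark about rating in knowledge of the arm is attached to the primary outcome, which is defined at 6 months, and does not mention baseline. This objection stands, and limits the point to what the schedule permits.

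**The layout may be the only fault.** Allocation at timepoint 0 and the 0-week column are nominally the same time. Baseline data describes demographics as collected at baseline, yet Table 2 lists them under Enrolment. Site procedures, which are not shown, may fix the order. This is possible. But the order that the article does state is the less protective one, and nothing in it says otherwise.

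**The size is hypothetical.** This is correct. The shift has no source and no known direction, and the slope of 0.73 joins SDs pooled from two small samples to a correlation from a third study. A reader might also take the word change in the outcome definition to mean that the full shift enters the result. That would hold for an unadjusted change score. It does not hold for the planned regression: with baseline as a covariate, the treatment effect is the same whether the dependent variable is the score or its change.

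**Not every baseline measure is exposed.** Observer POSAS and colour are assessed blind, so the self-rating mechanism does not reach them directly. Baseline also precedes laser, so treatment itself cannot affect it.

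**Conclusion.** The point holds as a defect in the schedule. Table 2 puts the patient-completed baseline after allocation, no section requires it earlier, and the main model adjusts for it. Contamination is permitted, not shown.

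Its size cannot be derived from the documents. Under an assumed 2-point allocation-driven difference, the adjusted effect would move by about 1.1 points (equal SDs) to 1.5 points (pooled SDs), which is 18% to 24% of the 6-point target. The direction could favour either arm. These figures rest on the correlation of 0.545 that the plan cites, on no carry-over of the shift to 6 months, and on the assumed shift itself. If participants in practice complete the forms before randomisation, or before they learn the arm, there is no bias by this route and only the table and text need correcting.

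Either way it should be settled before the first participant is randomised. The Study status section describes recruitment as imminent.

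**What to change.** - In Table 2, move the 0-week patient POSAS, CARe, SF-12 and self-reported resource use to a baseline column ahead of Allocation. Ideally move observer POSAS and colour with them; these are less exposed because they are blinded, but a single pre-allocation baseline is cleaner.
- Add one sentence to Concealment mechanism or Data collection methods: the patient-completed baseline forms are finished at the first visit before randomisation is requested.
- Optionally, add a field to the randomisation form confirming that they are complete.

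The cost is a small constraint on the order of steps at an existing visit, plus a minor change to the web system if the confirmation field is used. No visit is added, and the sample size (120 analysed, 150 recruited) and the analysis model are unchanged.
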